**Adverse Events**

An adverse event (AE) is any untoward medical occurrence in a clinical investigation subject administered a medicinal product and which does not necessarily have a causal relationship with this treatment. An AE can therefore be any unfavorable and unintended sign, symptom, or disease temporally associated with the use of a medicinal product, whether or not considered related to the medicinal product. Pre-existing events, which increase in severity or change in nature during or as a consequence of use of a medicinal product in human clinical trials, will also be considered AEs.

Any medical condition or clinically significant laboratory abnormality with an onset date before the screening visit and not related to study procedures is considered to be pre-existing, and should be documented in the case report form.

Any AE (i.e., a new event or an exacerbation of a pre-existing condition) with an onset date after the screening visit up to the last day on study (including the follow-up, off study medication period of the study), should be recorded as an AE on the appropriate CRF page(s).

An AE does not include:

- Medical or surgical procedures (e.g. surgery, Endoscopy, tooth extraction, transfusion); the condition that leads to the procedure are an adverse event.
- Pre-existing diseases or conditions or laboratory abnormalities present or detected prior to the screening visit that does not worsen.
- Situations where an untoward medical occurrence has not occurred (e.g. hospitalization for elective surgery, social and/or convenience admissions).
- Overdose of either study drug or concomitant medication without any signs or symptoms unless the subject is hospitalized for observation.

***Assessment of Adverse Events***

All AEs will be assessed by the investigator and recorded on the appropriate CRF page, including the date of onset and resolution, severity, relationship to study drug or study procedures, outcome and action taken with study medication.

The relationship to study drug therapy or study procedures should be assessed using the following definitions:

**No**: Evidence exists that the adverse event has an etiology other than the study drug or study procedures (e.g. pre-existing condition, underlying disease, intercurrent illness, or concomitant medication).

**Yes**: A temporal relationship exists between the event onset and administration of the study drug or between the event and the study procedures. It cannot be readily explained by the subject’s clinical state or concomitant therapies and, in the case of the study drug, appears with some degree of certainty to be related based on the known therapeutic and pharmacologic actions or adverse event profile of the study drug. In case of cessation or reduction of the dose, the event abates or resolves and reappears upon re-challenge. It should be emphasized that ineffective treatment should not be considered as causally related in the context of adverse event reporting.

These criteria in addition to good clinical judgment should be used as a guide for determining the causal assessment. If it is felt that the event is not related to study drug therapy, then an alternative explanation should be provided.

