**Brain functional Imaging - SPECT imaging and Analysis**

Single photon emission computed tomography (SPECT) will be conducted before and after HBOT. Subjects will lay supine in a quiet dimly lit room for 20 min prior to injection of the radiopharmaceutical. Apart from administration of the injection by a physician, they will remain alone in the room during this period. Subjects will be asked to remain at rest for 10 min after the injection of the radiopharmaceutical to allow uptake of the radiopharmaceutical in the brain.

An injection of 925-1110 MBq (25-30 mCi) of technetium-99m ethyl cysteinate dimmer (Tc-99m-ECD) will be given into an arm vein through a previously placed intravenous cannula. SPECT imaging of the brain will be performed, at 40-60 min post injection, with the subject’s head supported by a headrest, using a dual detector gamma camera (ECAM or Symbia T, Siemens Medical Systems) equipped with high resolution collimators. Data will be acquired in the step-and-shoot mode, using a 360 degree circular orbit, with the detectors of the gamma camera as close as possible to the subject’s head. The camera used for imaging will be noted for each subject and the same camera will be used for the follow-up study. Data will be acquired using a 128׳128 image matrix in 3 degree steps of 20 seconds per step. Data will be reconstructed by iterative reconstruction with no filtering. The Chang method (*μ*=0.12/ cm) will be used for attenuation correction.

Intra subject visual analysis will be conducted using a process in which pre and post treatment studies are fused and normalized to pre-treatment whole brain activity.

Visual analysis will be carried out by two nuclear medicine physicians who compared the scans independently and grad them as either: 1=no change, 2=mild change and 3=significant change. Where, no change is assign when no visual difference is noted in the number or size of perfusion deficits, mild change is given when a reduced number of perfusion defects are noted or the size of the perfusion defects is reduced. Significant change should be attributed when a global perfusion increment is observed in addition to diminution of defect numbers or size. Differences in evaluation will be resolve after reviewing the images together. Scan visual interpretation will be carried out while blinded to any laboratory or clinical data.

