## Statistical Analysis

### Safety Analysis

Adverse events will be tabulated by treatment group, severity and relation to treatment.

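### One relatedness definition covers study drug and study procedures together, so events from the SPECT injection can be counted as HBOT-related in the safety table

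*Protocol*

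**What the plan says.** In the Protocol, Assessment of Adverse Events, the investigator records for each event, among other things, the "relationship to study drug or study procedures, outcome and action taken with study medication". The section then gives one set of definitions for both causes: "The relationship to study drug therapy or study procedures should be assessed using the following definitions".

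- **No** applies when "Evidence exists that the adverse event has an etiology other than the study drug or study procedures".
- **Yes** begins "A temporal relationship exists between the event onset and administration of the study drug or between the event and the study procedures". It goes on to require that the patient's clinical state and concomitant therapies do not readily explain the event. One further criterion is confined to the drug: "in the case of the study drug, appears with some degree of certainty to be related".
- The section closes with "If it is felt that the event is not related to study drug therapy, then an alternative explanation should be provided".

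The Safety Analysis section is one sentence: "Adverse events will be tabulated by treatment group, severity and relation to treatment". Procedures are not mentioned there.

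The imaging section describes a procedure with its own potential for adverse events: the tracer "will be given into an arm vein through a previously placed intravenous cannula".

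**The concern.** The Objectives section promises an evaluation of the safety of HBOT in this population. The only relatedness judgement that the protocol defines does not isolate HBOT, because it asks about the study drug or the procedures in one breath. The safety table uses a third term, treatment, and nothing connects it to that judgement.

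If the combined answer feeds the table, harms of the scan and harms of HBOT fall in the same column. The mixing would not be even across groups. The cross group is scanned three times and the treated group twice, and the table is broken down by group. It could also show related events dated before the patient had entered the chamber. Because this is a rule for data capture, a distinction that is not recorded at the time is hard to recover later.

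**Working it through.** The protocol states no figure on this point. The check is a reading of the text followed by a count from the visit schedule.

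**Step 1: how an injection-site event is coded if the definitions are followed literally.**

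- No requires a cause other than both the drug and the procedures. An event caused by the injection has a procedure as its cause, so No is not available.
- Yes can be entered through the procedure limb. The next condition, no ready explanation in clinical state or concomitant therapy, does not exclude it, since a study injection is neither. The criterion on known drug effects applies only to the drug.
- The event is therefore a Yes.

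**Step 2: what the table does with it.** The Safety Analysis section asks for relation to treatment. No other relatedness assessment is defined, and no derivation is given. A combined Yes can pass into the table as treatment-related.

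**Step 3: whether such events can arise before HBOT.** The Study protocol section gives the treated group two evaluations (baseline, and after HBOT). It gives the cross group three (baseline, after the untreated period, and after HBOT), with the crossing after the second. Brain SPECT is part of the evaluation. Taking one injection per scan:

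| | Injections | Before first HBOT session | After the HBOT course |
|---|---|---|---|
| Treated patient | 2 | 1 | 1 |
| Cross patient | 3 | 2 | 1 |
| 1:1 pair | 2 + 3 = 5 | 1 + 2 = 3 | 1 + 1 = 2 |

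Share before any HBOT: 3/5 = 60% per pair, made up of 1/2 = 50% in the treated group and 2/3 = 67% in the cross group. Exposure to the injection is 3/2 = 1.5 times as high per cross patient.

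**Step 4: whether the recording window or the analysis set removes them.** The Adverse Events section records events with onset after the screening visit, which takes in the period before HBOT. The Safety Analysis Set is every subject in whom study treatment was started. That is a rule about subjects and not about periods, so a cross patient who goes on to HBOT brings the untreated period along.

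**Step 5: what can be separated afterwards.** Onset dates can identify events that precede the first session, that is, those from 3 of the 5 injections. They cannot do so for the other 2 of 5, which follow the HBOT course.

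**The case against.** The strongest reply is that the protocol already asks for a judgement specific to the drug. Yes has a criterion for the drug alone, and an alternative explanation is required when an event is thought unrelated to drug therapy. The criteria are a guide to be used with clinical judgement. Onset dates are collected, and many injection-site events can be recognised from their description. On this view the table already names the right quantity, and its derivation belongs to the SAP and the CRF.

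Much of this stands, and it keeps the point small. It does not dispose of it. The drug-only criterion leaves the procedure limb of Yes open. The alternative explanation feeds no category in the table. Dates do not help with scans after the course. A SAP can only derive what the CRF has captured.

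Several stronger readings are tempting and are not supported:

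- **That the CRF has a single field.** The CRF is not shown. The protocol shows one set of definitions, which is less than that.
- **That scan events will be reported as HBOT-related.** They can be. The protocol never equates relation to treatment with the combined Yes.
- **That patients who never receive HBOT will appear with related events.** They are outside the safety set, if the table uses that set, which the Safety Analysis section does not state. The point concerns events before HBOT in patients who later start it.
- **That study drug really denotes the tracer, as the only drug given.** Oxygen at pressure may itself be regarded as a drug, and the section names procedures separately. The term is ill-fitting, but it is not shown to point at the wrong thing.
- **That a number of miscoded events can be stated.** The sample-size section does not say whether its N of 31 is the total or per group, and the protocol gives no event rate for the injection.

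**Conclusion.** The point holds as a minor defect in safety reporting. One relatedness definition merges study drug and procedures, the table uses another term, and nothing links them. Events caused by the SPECT cannula or injection can therefore be counted as HBOT-related, including events before HBOT in patients who later receive it.

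Its size is best given as the share of injections that come before that patient's first session: 3 of 5 per 1:1 pair of completers. This assumes that every scheduled evaluation includes a scan, that both patients complete, and that the baseline scan follows the screening visit, whose place in the schedule is not given. It is a share of injections and not a count of events, and the expected number of such events is likely to be small. The primary efficacy analysis, the sample size and the success rule are unaffected.

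**What to change.** In Assessment of Adverse Events, replace the combined judgement by two yes/no items, each with its own definition: related to HBOT, and related to a study procedure (for example the SPECT injection). Write HBOT wherever the section now says study drug or study medication.

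In Safety Analysis, state that relation is tabulated from the HBOT item, and show procedure-related events in a separate table.

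The cost is one CRF tick-box and one table, with no extra visits or staff.

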***Serious Adverse Events***

**A** **serious adverse event** (SAE) is defined as follows:

Any adverse drug experience occurring at any dose that results in any of the following outcomes:

- Death;
- Life-threatening situation (subject is at **immediate** risk of death);
- In-patient hospitalization or prolongation of existing hospitalization (excluding those for study therapy or placement of an indwelling catheter, unless associated with other serious events);
- Persistent or significant disability/incapacity;
- Congenital anomaly/birth defect in the offspring of a subject who received study drug;

Other: medically significant events that may not result in death, be immediately life-threatening, or require hospitalization, may be considered a SAE when, based upon appropriate medical judgment, they may jeopardize the Subject and may require medical or surgical intervention to prevent one of the outcomes listed in this definition.

Examples of such events are:

- Intensive treatment in an emergency room
- Blood dyscrasias or convulsions that do not result in hospitalization
- Development of drug dependency or drug abuse

The investigator should notify the Institutional Review Board (IRB) or Independent Ethics Committee (IEC) as soon as is practical, of serious events in writing where this is required by local regulatory authorities, and in accordance with the local institutional policy.

